## **1. BACKGROUND**

### **1.1. General Information**

#### **Study title**

Low-interventional study of the aerosol combination therapy for pre-exposure prophylaxis of the novel coronavirus infection COVID-19

#### **Study type**

Low-interventional study (Order of the Government of the Russian Federation of April 3, 2020, No. 441 "On the aspects of the circulation of drugs for medical use intended for application in the conditions of risk, occurrence, and liquidation of an emergency situation and for the organization of medical assistance to persons affected by the emergency, prevention of emergency situations, prevention and treatment of the diseases that pose a threat to public health, diseases and injuries resulting from adverse chemical, biological, and radiation factors").

#### **Study code**

MIBVD-19

#### **Study phase**

Not applicable. Pilot study.

#### **Ethical considerations**

The study will be conducted in accordance with the Protocol and the legislation currently in force in the Russian Federation and is regulated by the following normative documents, as well as the available addendums and explanations to these documents:

- The Constitution of the Russian Federation;
- Federal Law of April 12, 2010, No. 61-FZ "On Circulation of Medicines";
- Federal Law of November 21, 2011, No. 323-FZ "On the Fundamentals of Public Health Protection in the Russian Federation";
- National Standard of the Russian Federation GOST R52379-2005 "Good Clinical Practice";
- Order of the Government of the Russian Federation of April 3, 2020, No. 441 "On the aspects of the circulation of drugs for medical use intended for application in the conditions of risk, occurrence, and liquidation of an emergency situation and for the organization of medical assistance to persons affected by the emergency, prevention of emergency situations, prevention and treatment of the diseases that pose a threat to public health, diseases and injuries resulting from of adverse chemical, biological, and radiation factors";
- Temporary guidelines of the Ministry of Health of the Russian Federation on the prevention, diagnosis, and treatment of the novel coronavirus infection (COVID-19) in the current edition;
- Federal Law of July 27, 2006, No. 152-FZ "On personal information";
- Order of the Ministry of Health of the Russian Federation of November 29, 2012, No. 986n "On approval of the Regulation of the Ethics Council";

- Order of the Ministry of Health of the Russian Federation of December 27, 2012, No. 1570 "On the Composition of the Ethics Council";
- Order of the Ministry of Health of the Russian Federation of April 1, 2016, No. 200n "On approval of the Rules of Good Clinical Practice";
- Eurasian Economic Commission Council Decision dated November 3, 2016, No. 79 "On approval of the Rules of Good Clinical Practice of the Eurasian Economic Union";
- Helsinki Declaration in its current version (Fortaleza, 2013).

## 1.2. **Rationale for Use of Combination Medication**

**In December 2019**, an outbreak of a novel coronavirus infection was identified in the People's Republic of China (PRC) with an epicenter in Wuhan (Hubei province). A previously unknown single-stranded RNA virus from the Coronaviridae family and the  $\beta$ -CoV genus was detected by sequencing in samples obtained from patients with pneumonia (ZhuN. et al., 2020). On February 11, 2020, the International Committee on Taxonomy of Viruses designated the official name to the pathogen SARS-CoV-2. The World Health Organization (WHO) on February 11, 2020, announced the official name of the disease caused by the novel coronavirus COVID-19 ("Coronavirus disease 2019"). SARS-CoV-2 is included in the list of diseases that pose a threat to public health (Order of the Government of the Russian Federation of January 31, 2020, No. 66). Many aspects of coronavirus infection pathogenesis require further comprehensive study. Currently, there are no proven effective clinical protocols for the prevention and treatment of COVID-19 infection.

**Members of the coronavirus family** were previously regarded as agents present in the structure of acute respiratory viral infections causing mild or moderate upper respiratory tract disorders (with extremely rare lethal outcomes). At the end of 2002, SARS-CoV coronavirus emerged as the etiological agent of atypical pneumonia that caused severe acute respiratory syndrome (SARS) in humans. Overall, during the 2002–2004 epidemic, more than 8000 cases in 37 countries were registered, of which 774 were fatal. A new MERS-CoV coronavirus, the causal agent of Middle East respiratory syndrome, emerged in 2012. Until January 31, 2020, 2519 cases of coronavirus infection caused by this virus were registered, 866 of which were fatal (82% of cases were reported in Saudi Arabia).

**The source of COVID-19 infection** is a sick person, including one who is in the incubation period of the disease. The infection is transmitted through respiratory droplets, airborne transmission, and contact routes. The entrance pathway of SARS-CoV-2 is the epithelium of the upper respiratory tract, stomach and intestines. The initial stage of infection is the penetration of the pathogen into target cells (mainly pulmonary alveolar type II cells) that have angiotensin-converting enzyme 2 (ACE2) receptors. SARS-CoV-2 can disseminate from the systemic circulation into other organs or across the cribriform plate of the ethmoid bone to the CNS. COVID-19 is confirmed if laboratory testing of biological samples for the presence of SARS-CoV-2 RNA using nucleic acid amplification techniques gives a positive result, regardless of clinical symptoms. The incubation period for COVID-19 infection lasts between 2 and 14 days, with an average of 5–7 days.

**The initial clinical manifestations** are similar to those of other acute respiratory infections (body temperature above 37.5°C and one or more of the following symptoms: dry cough or cough with sparse sputum; shortness of breath; feeling of congestion in the chest; oxygen saturation of blood according to pulse oximetry ( $SpO_2$ )  $\leq$  95%; sore throat, runny nose, and other catarrhal symptoms; weakness; headache; anosmia; diarrhea) in the absence of other known reasons that explain the clinical picture,

regardless of the epidemiological history. The early symptoms may include myalgia (11%), mental confusion (9%), headaches (8%), hemoptysis (5%), diarrhea (3%), nausea, vomiting, and heart palpitations. At the onset of infection, these symptoms can also be observed in the absence of fever. Eighty percent of patients experience a mild form of acute respiratory viral infection, and 20% of confirmed cases are severe.

**The most common complication** of COVID-19 is bilateral pneumonia with the following typical manifestations observed on computed tomography or chest radiography images of the lungs: a decrease in pneumatization of the lung tissue manifested as ground-glass opacity with or without consolidation and with or without thickening of the interlobular septa ("cobblestone" appearance); multiple sites of decreased pneumatization of lung tissue manifested as a rounded shape ground-glass opacity with or without consolidation and with or without thickening of the septa ("cobblestone" appearance); a reverse halo or other signs of organizing pneumonia (at the later disease stages); predominantly peripheral localization; and bilateral nature of the disorder. Radiological signs of inflammatory lesions on computed tomography images may be absent in 18% of patients with a mild condition and in 3% of patients in a moderate/severe state, as well as in the early stages of the disease.

**Severe forms** of COVID-19 develop mainly in elderly patients (65 years or older). Among patients, concomitant diseases are often observed: diabetes mellitus (20%), arterial hypertension (15%), and other cardiovascular diseases (15%). In severe cases, a rapidly progressing lower respiratory tract infection, pneumonia, acute respiratory failure, ARDS, sepsis, and septic shock are often observed. Acute respiratory distress syndrome (ARDS) has been reported to develop in 34% of patients. Hypoxemia (a decrease in SpO2 below 88%) develops in more than 30% of patients. The most severe dyspnea develops on the 6th-8th day after the infection.

**Previous clinical experience** in managing patients with SARS associated with SARS-CoV and MERS coronaviruses defines generally accepted approaches to the treatment of COVID-19 that consist of proactive treatment prior to the development of a complete complex of life-threatening symptoms. Medical care provided to the patients includes monitoring to detect signs of worsening in their clinical condition. Patients infected with SARS-CoV-2 receive supportive pathogenetic and symptomatic treatment. Several drugs are outlined for the treatment of COVID-19: chloroquine, hydroxychloroquine, mefloquine, lopinavir+ritonavir, tocilizumab, azithromycin (in combination with hydroxychloroquine), and recombinant human interferons  $\beta$ -1b and  $\alpha$ -2b. Drugs in the clinical trial phase for the treatment of patients with COVID-19 include umifenovir, remdesivir, and favipiravir. However, the currently available information on the results of treatment with all of these drugs does not provide an unambiguous conclusion about their effectiveness or ineffectiveness.

**The antiviral mechanisms of medications** that are considered promising in the treatment of COVID-19 mainly include nonspecific (inhibition or activation) or specific (inhibition) effects on the immune system: 1) antimalarial drugs - nonspecific inhibition of the biosynthetic processes of proteins and RNA/DNA by increasing the lysosomal pH in both epithelial cells and immunocompetent cells that can inhibit the penetration of the virus into the cell and its replication and determines the anti-inflammatory and immunosuppressive effects; 2) antiretroviral drugs - nonspecific inhibition of cellular RNA/DNA biosynthesis by inhibiting reverse transcriptase, proteases, and other enzymes in the cells and tissues of the body that are characterized by active proliferation; 3) interferon drugs - nonspecific activation of cellular and humoral immunity with an increase in cytokine production, suppression of proliferation and acceleration of apoptosis in immunocompetent cells; 4) tocilizumab - a specific inhibition of IL-6 receptors for the rapid and effective suppression of immunity in order to eliminate the life-threatening symptoms of the cytokine release syndrome in patients with a moderate to severe disease state.

**A significant side effect** of antimalarial drugs is cardiotoxicity. A randomized controlled trial showed that the treatment of a disease caused by SARS-CoV-2 with lopinavir+ritonavir monotherapy did not shorten the duration of hospitalization and was not more efficient than regular symptomatic therapy. Before the etiological diagnosis is confirmed, it is recommended to include intranasal forms of interferon- $\alpha$ 2b, interferon-inducing agents, and broad-spectrum antiviral drugs, such as umifenovir, in the treatment. However, objective evidence of the efficacy of the above medicinal products in the case of COVID-19 is missing. The use of medicinal products specifically blocking pro-inflammatory cytokines requires cautious consideration of the risk-to-benefit ratio for the patient.

Many countries are currently working on the development of several types of vaccines for **specific prophylaxis of COVID-19**; nevertheless, at present, there are no approved drugs. Nonspecific preventive activities mainly comprised preventing the importation and spread of COVID-19 and are applied to the source of infection (a sick person), the mechanism of pathogen transmission, and the potentially susceptible contingent (protection of individuals who are and/or were in contact with a sick person).

**Pre-exposure prophylaxis** of COVID-19 is recommended as an intranasal administration of recombinant interferon- $\alpha$ 2b for healthy individuals. For postexposure prophylaxis in individuals with a single contact with a confirmed case of COVID-19, as well as in individuals in a focus of infection, pharmaceutical prophylaxis with chloroquine, hydroxychloroquine, and mefloquine is recommended, despite their cardiotoxicity. There are currently no proven protocols for effective therapeutic prophylaxis of COVID-19.

**From the pathophysiological point of view**, for the development and application of efficient prevention and treatments of COVID-19, a number of previously published data on the genetic and molecular mechanisms of SARS-CoV-2 interaction with target cells are important. According to these data, a main step of COVID-19 pathogenesis is assumed to be the dose and duration of the viral effect on ventilation-perfusion regulation of the peripheral parts of the bronchopulmonary system rather than virus replication itself with epithelial cell damage and an induced immune system response.

**J.K. Millet & G.R. Whittaker (2018)** proposed a model for the penetration of a cell by SARS-CoV and coronaviruses in general. The model combines various activators and triggers of the viral S-protein as follows: 1) S-protein cleavage by a protease at the binding site of S1 and S2 domains, which provides a preliminary stage of priming; 2) receptor interaction; 3) cleavage of the S2 domain by a protease to release viral fusion peptides; 4) ion changes that contribute to conformational changes and insertion of fusion peptides, caused not only by H+ ions but also by Ca2+ ions, which are necessary for fusion peptide insertion into the lipid bilayer of the cell membrane.

**A comparative study of genomes of the viruses** identified 380 amino acid substitutions between SARS-CoV-2 and SARS-CoV (SARS-like coronaviruses), which may have caused a functional and pathogenic divergence of SARS-CoV-2 (Wu A. et al., 2020). A similarity was found between the external part of the SARS-CoV-2 and SARS-CoV S-protein S1 domains, suggesting that these viruses can use membrane ACE2 as a penetration point into the target cell (Lu R. et al., 2020). Furthermore, it was confirmed by cryo-electron microscopy and surface plasmon resonance methods that both viruses use the ACE2 receptor to enter the cell and employ the serine protease TMPRSS2 with ATP for S-protein priming (Hoffmann M. et al., 2020; Wrapp D. et al., 2020). Using molecular simulation methods, it was calculated that ACE2 has two orders of magnitude greater binding to SARS-CoV-2 than to SARS-CoV (Ortega J.T. et al., 2020).

**ACE2 is a membrane enzyme** with an active center located on the surface of type 2 alveolar cells, arterial and venous endothelial cells, smooth muscle cells of the lungs and many other organs (Hamming I. et al., 2004). It mainly acts as a counterweight to the angiotensin-converting enzyme (ACE), which catalyzes the conversion of angiotensin I into the vasoconstrictor hormone angiotensin II. In this regard, it is interesting that in recent clinical observations of patients with severe COVID-19, a high incidence of concomitant diseases such as hypertension and type I or type II diabetes was noted; for the treatment of these diseases, inhibitors of circulating ACE and/or angiotensin I receptor antagonists are used, which increase the expression of ACE2 (Fang L., Karakiulakis G., Roth M., 2020), and this, in turn, can increase the susceptibility of such patients to infection with the SARS-CoV-2 virus.

**Based on the known data** on the physiological role of ACE2 and the extremely high affinity of the SARS-CoV-2 virus, we can assume the following picture of the pathogenesis of this viral infection that defines not only the clinical course of COVID-19 but also the most effective means and methods of active pharmaceutical prophylaxis of this infectious disease. When the SARS-CoV-2 virus contacts the mucous membrane of the tracheobronchial tree, the SARS-CoV-2 viral envelope glycoprotein has a high-affinity interaction with the ACE2 active centers on the apical surface of all available cells, including epithelial cells, alveolar cells, alveolar macrophages, and other cellular elements. Further stages of virus penetration, including immersion of the SARS-CoV-2 + ACE2 complex inside the cell and the beginning of viral RNA replication, are virtually determined and relatively fast processes. Moreover, the amount of the viral load at the time of infection will largely determine the degree of simultaneous functional suppression of ACE2 bronchodilating and vasodilating activity and the relative functional prevalence of ACE constrictor activity in the walls of the bronchi and alveoli.

**The biosynthesis of all membrane proteins** in cells is continuous, but it cannot be replenished earlier than within a few hours after infection with SARS-CoV-2, during which peripheral parts of the lungs will exhibit increased hypoxic processes and disturbances in the ventilation and perfusion properties associated with a reduction in the smooth muscle cells of blood vessels and bronchi. The outcome of subsequent pathogenetic events will largely depend on the duration and reversibility of physiological changes at this stage. Thus, incomplete restoration of ACE2 expression after infection with SARS-CoV-2 with continued synthesis and dissemination of viral particles alongside vaso- and bronchoconstriction during the incubation period will determine a further increase in hypoxic and metabolic changes in the anatomical structures of the blood-air barrier, including the basement membrane and interstitial tissue, thus enhancing the constrictive effects and closing the "vicious circle" of the pathogenesis of destructive inflammatory changes in the lung tissue. Even with a clinically asymptomatic course of the infectious process, these changes, increasing in the peripheral parts of the lung at 7-14 days or earlier, can cause respiratory failure and a decrease in pneumatization of the lung tissue manifested as ground-glass opacity on radiological images, as well as other symptoms characteristic of typical pneumonia with COVID-19.

**The potential efficiency** of vasodilating agents against the virus can be confirmed by the results of clinical trials of camostat mesylate, a serine protease TMPRSS2 inhibitor, which lowers blood pressure by reducing the activity of protease inhibition of epithelial sodium channels (Kitamura K., Tomita K., 2012), efficiently blocks the penetration of the virus into the cell, and is therefore considered a potential antiviral treatment option for COVID-19 (Hoffmann M. et al., 2020). In addition, data on possible inhibition of the penetration of the SARS-CoV virus into cells by the antiarrhythmic medication amiodarone appear to be relevant (Stadler K. et al., 2008).

**For effective pharmaceutical prophylaxis of COVID-19**, among the medicinal products that appear to be promising for application in healthy individuals, combination medicinal products that improve metabolic and redox processes in the cells of the bronchopulmonary system, exhibit antihypertensive and bronchodilating properties and are used in minimally effective doses to exclude possible toxic and side effects should be considered. Examples of these agents are antioxidants (glutathione, ubiquinone, superoxide dismutase), metabolic precursors and regulators of ATP synthesis (inosine, nicotinamide), direct or indirect regulators of ion channels in the membranes of epithelial and smooth muscle cells (potassium and/or magnesium medicinal products, furosemide),  $\beta$ -adrenergic agonists, myotropic antispasmodics, and inducers of the endogenous synthesis of nitric oxide.

**To reduce the clinical manifestations** after the contact of the SARS-CoV-2 virus with the cells of the tracheobronchial tree, as well as to increase the efficacy of local exposure and minimize the systemic side effects of medicinal products in healthy individuals, the aerosol administration of aqueous solutions of medicinal products appears to be the most appropriate method of application. For example, it was previously shown in observational studies on healthy volunteers that inhaled furosemide in low concentrations (up to 40 mg) has a relaxing effect on smooth muscle cells of the airways of the human lungs due to the same mechanism as in the cells of the loop of Henle (Bianco S. et al., 2000; Inokuchi R. et al., 2014; Spicuzza L. et al. 2003; Cavliere F., Masieri S., 2002; Masoumi K. et al., 2014) and may also exhibit immunostimulant properties (Bialasiewicz P. et al., 2004).

## **2. STUDY ASSESSMENT**

### **2.1. Objective**

To assess the efficacy and safety of aerosol combination therapy for the pre-exposure prophylaxis of COVID-19 in healthy volunteers at high risk of exposure to SARS-CoV-2 infection.

### **2.2. Endpoints**

- 3.2.1 Determine the frequency of laboratory confirmed SARS-CoV-2 cases, defined by RT-PCR positivity within 28 days observational period, in high risk population with routine COVID-19 positive contacts.
- 3.2.2 Evaluation of the safety of aerosol combination therapy as the pre-exposure prophylaxis for COVID-19.

### **2.3. Design**

The study is intended as a low-interventional prospective open-label clinical study of aerosol combination therapy in a cohort of healthy adult volunteers regularly exposed to COVID-19 positive contacts.

### **2.4. Population**

This is an open-label study is intended to obtain preliminary estimates in healthy adults of the efficacy and safety of the combination medication. Based on the observational trials in high risk individuals exposed to routine COVID-19 positive contacts frequency of SARS-CoV infection confirmed by RT-PCR is 11.1% (García I.S. et al., 2020). We expect that the investigated pre-exposure prophylaxis allows to eliminate SARS-CoV-2 positive cases to 3% or less during observational period. With Alpha error rate of 0.05, beta error 0.85, we need to include 96 subjects.

Rare adverse events (AEs) are not demonstrable in a clinical study of this size. With the assumption that all enrolled subjects will likely complete the treatment and safety visits in this relatively short duration study, the following statistical considerations apply. With 100 subjects in the treatment group, the chance of observing at least one AE of probability 5% or more is approximately 95%. Therefore, if no AEs of a given type occur, we can be relatively confident that they will occur in fewer than 5% of people.

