## 6. STATISTICAL ANALYSIS

The methods for statistical analysis of the obtained data are determined by the nature, type, and distribution of the data. The applicability of a number of statistical methods will be evaluated upon the completion of the data collection due to the unknown distribution, sample uniformity, etc. In the course of the analysis, the list of methods used can be expanded if necessary for high-quality data processing.

Statistical processing of data obtained in the study will be carried out using statistical programs or other special software that would ensure high quality of the results. Interval (quantitative) data will be described using the arithmetic mean, standard deviation, median, lower (25%) and upper (75%) quartiles, minimum and maximum values. Categorical (qualitative) data will be described using absolute and relative frequencies. To compare normally distributed quantitative data, standard parametric criteria shall be employed: Student's t-test for dependent/independent samples and analysis of variance (ANOVA) for repeated measurements. For the comparison of quantitative data that are not normally distributed, standard nonparametric tests shall be employed. The frequencies of the variables will be compared between the groups using Pearson's  $\chi^2$  test or Fisher's exact test.

AEs will be analyzed based on the frequency of adverse events/serious adverse events. Adverse events registered within the study will be presented by incidence rate (the number of patients with AEs and the number of such AEs in the group). AEs will also be presented by their intensity and relationship with the administration of the combined medicinal product.

Regardless of the reason for the termination of the study, the data of all enrolled healthy volunteers will be taken into account when analyzing the efficiency and safety of the investigational therapy.

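### Section 2.4 prints power as beta, and the frequency tests named in Section 6 need a second group and are not the basis of the 96

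*Protocol*

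**What the plan says.** - **Sample size (Protocol, 2.4 Population).** An outside observational source is cited for the reference rate: "frequency of SARS-CoV infection confirmed by RT-PCR is 11.1"%. The sponsor expects that the prophylaxis "allows to eliminate SARS-CoV-2 positive cases to 3% or less during observational period". The conclusion is "With Alpha error rate of 0.05, beta error 0.85, we need to include 96 subjects". Neither the test nor its sidedness is named.
- **Design (Protocol, 2.3 Design).** The study is a "low-interventional prospective open-label clinical study of aerosol combination therapy in a cohort" of healthy adult volunteers. No control group or allocation ratio is defined.
- **Primary endpoint (Protocol, 2.2 Endpoints and 5.1 Efficiency).** It is binary: RT-PCR positivity within the 28-day observation period.
- **Analysis (Protocol, Section 6 Statistical Analysis).** For categorical data the plan gives absolute and relative frequencies as description. For comparison it says "The frequencies of the variables will be compared between the groups using" Pearson's chi-square or Fisher's exact test. For quantitative data it lists paired and independent t-tests, repeated-measures ANOVA and nonparametric tests. It also says "The applicability of a number of statistical methods will be evaluated upon the completion of the data collection", giving unknown distribution and sample uniformity as reasons, and allows methods to be added.

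**The concern.** Two statements do not fit the design they describe.

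First, "beta error 0.85" contradicts the number printed beside it. Read literally, it says the study has a 15% chance of detecting the effect it expects, and 96 does not follow from it. A reader who checks the power statement cannot tell from the text what was intended.

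Second, the 96 was obtained by setting one proportion against a fixed external rate, yet that comparison appears nowhere in Section 6. The frequency tests that do appear need a second group, which the protocol does not define. The stated power is therefore attached to an analysis that is not described, and the described comparison cannot be carried out on the primary endpoint within this cohort. What is at stake is whether the protocol's one efficacy comparison is identifiable from its own text.

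**Working it through.** **Inputs (all from Protocol 2.4):** p0 = 0.111, p1 = 0.03, alpha = 0.05, printed beta = 0.85, stated n = 96. Sidedness is not given, so both were tried.

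**Formula (one-sample proportion, normal approximation):**

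n = [z(1−α/2)·√(p0(1−p0)) + z(1−β)·√(p1(1−p1))]² / (p0−p1)²

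**Step 1: common terms.** √(0.111 × 0.889) = 0.3141; √(0.03 × 0.97) = 0.1706; p0 − p1 = 0.081.

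**Step 2: reproduce the 96 with beta 0.15 (power 85%), two-sided.**
[1.960 × 0.3141 + 1.036 × 0.1706]² / 0.081² = (0.7925 / 0.081)² = 95.7, so 96. This matches the protocol. Approximate power at n = 96 is 85.2%.

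**Step 3: take beta 0.85 literally (power 15%), two-sided.**
[1.960 × 0.3141 − 1.036 × 0.1706]² / 0.081² = (0.4389 / 0.081)² = 29.4, so 30. This does not match.

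**Step 4: could another calculation explain 96?**

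| Calculation | n |
|---|---|
| One-sample, two-sided, power 80% | 88 |
| One-sample, two-sided, power 90% | 107 |
| One-sample, one-sided, power 85% | 74 |
| As step 2, with continuity correction | 108 |
| As step 2, arcsine transformation | 82 |
| As step 2, null variance only | 136 |
| As step 2, alternative variance only | 40 |
| Two independent groups, two-sided, power 85% | 178 per group |

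Two further variants land near 96, but only at 90% power: arcsine two-sided (96) and one-sided with continuity correction (95). Neither uses the printed 0.85. The two-group row serves only to show that 96 is not a two-group number; no such design is in the protocol.

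**Step 5: what 96 delivers with an exact test.** With X ~ Binomial(96, p):
- P(X ≤ 4 | 0.111) = 0.0145 and P(X ≤ 5 | 0.111) = 0.0376, so at a lower-tail limit of 0.025 the test rejects at 4 or fewer cases.
- Power is P(X ≤ 4 | 0.03) = 0.838.
- The upper limit of the two-sided 95% Clopper-Pearson interval is 10.3% at 4/96 and 11.7% at 5/96. The interval and the test therefore agree on either side of 11.1%.

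**Step 6: set the sections side by side.** Section 2.4 sizes one proportion against a constant. Section 2.3 supplies one cohort. Section 6 compares frequencies between groups. The first two agree with each other; the third agrees with neither.

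**The case against.** The strongest reply is that little turns on this. The study calls itself a pilot, Section 2.4 speaks of preliminary estimates, and the endpoint is worded as determining a frequency. Section 6 already provides relative frequencies, so the main estimate can be produced without any test. A detailed choice of test and interval is often left to a statistical analysis plan, which may exist here. Much of this stands, and it rules out several stronger inferences that a reader might draw:

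- **That the study has only 15% power.** It does not. The 96 corresponds to about 85% power, so the error is in the label.
- **That Section 6 lists only between-group methods.** It also lists the dependent-samples t-test, repeated-measures ANOVA and descriptive frequencies, all usable in one cohort. The mismatch is confined to the comparison of frequencies.
- **That the primary question cannot be analysed at all.** The rate can be estimated as planned. What cannot be run is the named comparison.
- **That the primary test will be chosen after the count is seen.** The clause on late evaluation covers an unspecified number of methods and refers to distribution and sample uniformity; it does not single out the primary endpoint.
- **That the choice of method readily reverses the result.** At 5 of 96 a one-sided exact p is 0.038, while the two-sided p-values run from 0.066 to 0.075. That is mainly a difference in sidedness at one borderline count, which has about a 9% chance if the true rate is 3%, and the 96 already implies a two-sided test.

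The reply does not remove the core. Section 2.4 sets an alpha, a beta and a target rate, so it commits to a comparison. The protocol misstates one of those figures, and for that type of data Section 6 names tests that do not fit. These are errors in what the document says. They are not details left for later.

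**Conclusion.** The point holds in limited form. The power statement is wrong as printed: literally 15% power and about 30 subjects, against an evident intention of 85% power and 96 subjects (95.7 before rounding; 83.8% power with the exact test). For the binary primary endpoint, the only frequency tests named in Section 6 require a second group that the single-cohort design lacks, and they are not the basis of the 96.

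The sample size is unaffected, and nothing here shows the study to be too small for the one-sample comparison. That conclusion rests on four assumptions: 11.1% is treated as a fixed, known reference; the true rate on prophylaxis is 3%; all 96 subjects contribute a result; and the test is two-sided. The last is inferred from the match in step 2, because the protocol does not state it.

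**What to change.** - **Section 2.4.** Replace the power statement with: two-sided alpha 0.05, beta 0.15 (power 85% by normal approximation, about 84% exact), one-sample comparison of the 28-day RT-PCR positivity rate with 11.1%, assumed rate 3%, n = 96.
- **Section 6.** For the primary endpoint, replace the between-group tests with an exact binomial test against 11.1%, reported with a two-sided 95% Clopper-Pearson interval. State that this method is fixed before data collection ends, so that the general clause on late evaluation of methods cannot be read as applying to it.
- **Optional.** A formal success rule (4 or fewer cases of 96) is not needed. For a pilot, the interval set against 11.1% resolves the mismatch.

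The cost is wording in two sections. N, visits and data collection are unchanged.

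### Section 2.4 gives a beta error of 0.85, which contradicts N = 96; the 0.85 is evidently the power, mislabelled, and N itself stands

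*Protocol*

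**What the plan says.** All the planning inputs are in Protocol section 2.4 (Population). The reference rate is 11.1%, taken from a cited study of exposed individuals. The expectation under prophylaxis is that it "allows to eliminate SARS-CoV-2 positive cases to 3% or less during observational period". The error rates and the size follow in one sentence: "With Alpha error rate of 0.05, beta error 0.85, we need to include 96 subjects". No allowance for dropout is made, since the section assumes that "all enrolled subjects will likely complete the treatment and safety visits".

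Section 2.3 describes an "open-label clinical study of aerosol combination therapy in a cohort of healthy adult volunteers regularly exposed to COVID-19 positive contacts", so there is one group and no concurrent control. Section 2.2 sets the efficacy endpoint as infection "defined by RT-PCR positivity within 28 days observational period". The protocol gives no other beta or power for efficacy, in section 6 (Statistical Analysis) or elsewhere. It does not say whether alpha is one- or two-sided, or which test the calculation assumes.

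**The concern.** The beta error is the probability of missing the assumed effect when it is present. A value of 0.85 means power of 1 − 0.85 = 0.15. Nobody would plan a study on that basis, and the figure does not fit the sample size given in the same sentence. The wording does not rescue it: alpha and beta are both described there as errors, so the term cannot be read as power.

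What is at stake is the accuracy of the protocol's only justification for its size. A reader who takes the sentence literally gets the wrong operating characteristic. A reader who suspects a slip can confirm it only by back-calculating with a test and a sidedness that the text does not name.

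**Working it through.** **Inputs.** p0 = 0.111, p1 = 0.03 (difference 0.081), alpha = 0.05, beta as printed 0.85, N as printed 96 (all section 2.4). The one-sample comparison with a fixed 11.1% is inferred from the single-cohort design in section 2.3.

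**Formula.** One-sample proportion, normal approximation:

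n = [(z_alpha × √(p0(1−p0)) + z_power × √(p1(1−p1))) / (p0 − p1)]²

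with √(0.111 × 0.889) = 0.3141 and √(0.03 × 0.97) = 0.1706.

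**1. Reproducing 96.** Two-sided alpha 0.05 (z = 1.960) and power 0.85 (z = 1.036):

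n = [(1.960 × 0.3141 + 1.036 × 0.1706) / 0.081]² = 95.72, rounded up to **96**.

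This matches the printed N. Conversely, the approximate power at N = 96 is 85.2%.

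**2. The sentence as printed.** Beta 0.85 is power 0.15, so z_power = −1.036:

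- two-sided: n = [(1.960 × 0.3141 − 1.036 × 0.1706) / 0.081]² = 29.36, rounded up to **30**;
- one-sided: replacing 1.960 by 1.645 gives 17.61, rounded up to **18**.

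**3. Could another method give 96 at beta 0.85?** None of those tried does:

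| Method at power 0.15 | Subjects |
|---|---|
| Other one-sample approximations (null-only or alternative-only variance, arcsine, continuity correction) | 2 to 41 |
| Exact binomial, one-sided 0.05 | 26 |
| Exact binomial, one-sided 0.025 | 32 |
| Two-arm comparison, with or without continuity correction | 8 to 39 per arm, so at most 2 × 39 = 78 in total |

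**4. How firmly is beta 0.15 identified?** At power 0.85 with one-sided alpha 0.05, the formula gives 73.30, rounded up to 74, so 96 points to a two-sided alpha. Other routes come close. The two-sided arcsine formula at power 0.90 gives 95.82, also 96. The one-sided formula with continuity correction at power 0.90 gives 94.35, rounded up to 95. The formula above, one-sided at power 0.95, gives 96.89, rounded up to 97. All of these need a power that the protocol does not print. Of the combinations tried, only two-sided alpha with power 0.85 in the standard formula gives 96 and also uses the printed 0.85.

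**5. Exact binomial power at N = 96, for information.**

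| Alpha | Success if positives ≤ | Attained one-sided alpha | Power at 3% |
|---|---|---|---|
| Two-sided 0.05 (one-sided 0.025) | 4 | 0.0145 | 83.8% |
| One-sided 0.05 | 5 | 0.0376 | 93.1% |

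With 96 × 0.03 = 2.9 expected positives, the exact figures are a useful companion to the approximation.

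**The case against.** The best defence is that this is a swapped label. A power of 0.85 is conventional, it reproduces the printed N, and nothing in the enrolment, endpoint, design or analysis depends on the word. A statistician would guess the intention, and the protocol calls itself a pilot study seeking preliminary estimates. This stands as to size: it is an error of statement, and N is not undermined. It does not remove the error, because the printed beta and the printed N contradict each other.

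Several stronger readings might be inferred, and the document does not support them:

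- *That the trial has 15% power or is too small.* At 96 subjects and the protocol's own rates, the approximate two-sided power is 85.2%.
- *That 96 can arise only from beta 0.15.* The arcsine formula at power 0.90 also gives 96. Beta 0.15 is the best inference, but other solutions exist.
- *That exact power of 83.8% contradicts a claimed 85%.* The protocol claims no exact power, and 83.8% holds only if alpha is two-sided; under one-sided 0.05 it is 93.1%.
- *That leaving out the test and sidedness is itself an error.* Such detail is commonly left to a statistical analysis plan, which is not at hand. It matters here only because the corrected sentence has to be reproducible.
- *That a non-significant result could not be interpreted.* It would be read from the observed rate and its interval, whatever planning beta was printed.
- *That efficacy power should be assessed at 100 subjects.* That number belongs to the adverse-event statement in section 2.4.

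**Conclusion.** The point holds as a labelling error in the protocol's only efficacy power statement. As printed, "beta error 0.85" corresponds to about 30 subjects (18 if alpha is one-sided), and no method tried brings it to 96. Read as power 0.85, that is beta 0.15, the same inputs give 95.7 and hence 96.

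This rests on two assumptions that the protocol does not state: a one-sample comparison with a fixed 11.1%, which follows naturally from the single-cohort design, and a two-sided alpha, which is inferred from the match. That the printed beta is inconsistent with N depends on neither, since the one-sided and two-arm versions also fail to reach 96. The correction is small but worth making. The sample size does not need to change.

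**What to change.** Amend the sentence in section 2.4 to read, in substance: two-sided alpha 0.05, power 0.85 (beta error 0.15), one-sample comparison with the reference rate of 11.1%, expected rate 3%, N = 96. The sponsor should confirm the sidedness and the test against its own calculation before the text is fixed, because both are inferred here.

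Optionally, add that exact binomial power at 96 subjects is about 84% if alpha is two-sided, or about 93% if it is one-sided 0.05. This would be descriptive only; the correction need not write a rejection boundary into the protocol.

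The cost is one sentence. Enrolment, endpoint and analysis are unaffected.
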